#### Determination of Sample Size

A calculation of sample size was carried out with one case per one control, a power of 80%, an alpha risk of 5%, a global developmental delay (obtained with the BLR test) prevalence rate of 50% in the controls and 25% in the children on the program (based on INTERREG results). The result obtained is a sample of 58 people in the intervention group and 58 in the control group. Taking into account the potential loss of 10% of subjects over the course of this ongoing research, 64 subjects were originally recruited for the intervention group and 64 subjects in the control group.

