#### Sample Characteristics

- Eligibility criteria

There were two eligibility criteria: (i) the child was to have been born between September 2018 and December 2019 in the general population; and (ii) all families had their main residence in the *Pays Lunévillois*, in Lorraine, France.

- Exclusion criteria

There were three exclusion criteria: (i) a child born prematurely, before 37 weeks of pregnancy; (ii) families that did not speak French; (iii) non-settled traveler families, temporary refugees, and families with no fixed abode.

Participants were not prohibited from taking part in other research projects during this trial.

- Randomization (Figure 1)1) Every month, the PMI service sent the coordinating psychologist (SB) a list of all pregnancies reported in the population residing in the recruitment area, in the seventh month of pregnancy (on average 60 births per month).2) SB then sent a letter to all of the families on the list, informing them that research was being conducted and that they were likely to be contacted and invited to participate. This letter informed the families that they had 2 weeks to refuse participation.3) Two weeks later, SB performed the randomization process (Zelen randomization with a double consent for the 2 groups) based on the updated list of reported pregnancies post-refusal and returns for wrong address after the first letter had been sent. The families were thus randomly assigned to either the “intervention” or the “control” group.4) SB then sent a second letter informing families that they have been randomly selected to take part in the PERL study and forwarded a brochure describing the terms of participation (purpose of the study, how to participate, a presentation of the relevant stakeholders) with a suggested date for an HV (the start of the 8th month of pregnancy).5) If no refusal was received from the families, SB performed the HV to outline the trial to them, and if they agree to take part in the study they were asked to sign consent forms.

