#### Rate of Inclusion

The PMI nurses in the area have taken on the PERL system in addition to their normal workload. As a result, we have had to adapt the number of families followed by each nurse to match the resources allocated by the PMI service. The PMI nurses were able to take on up to four families each, with 16 PMI nurses taking part in total. The control group was recruited with the same number of participants each month in order to avoid any bias (seasonality, etc.) and so that SB could perform the evaluation HVs within the allotted time. When the expected number of families per month (1 per PMI nurse) was reached, recruitment then stopped for that month and resumed the following month. In practice we had to limit the number of study participants to 128 families to enable coordination and feasibility in the field.

The number of PMI nurses participating in the project changed over the months (from September 2018 to September 2019). There were 6 PMI nurses over the first 3 months, 9 the following 7 months, then 10 professionals from May 2019, and at least 16 from September 2019.

The maximum number of subjects recruited has therefore changed according to the number of professionals involved in the research, 16 professionals being the necessary number to recruit the entire population. Furthermore, for reasons outside the study, recruitment was interrupted for 4 months (January 2019 to April 2019).

If we had been able to involve the desired number of professionals at the start of the research, we would have reached our recruitment goals within 5 months.

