#### Comparative Analysis

The effects of the support will be assessed by comparison with the control group. The student's *t*-test will be used for the comparative analyses of the quantitative variables. The chi-squared (χ^2^*)* test will be used for the comparative analyses of the qualitative variables. We will also compare the basic characteristics of populations who refused to take part with those who agreed to be included in the study.

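### Arms were recruited in equal numbers each month, but the named chi-squared and t-tests ignore month: valid, mildly conservative if month matters, and cheap to improve

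*Protocol article*

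**What the plan says.** All references are to the protocol article.

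- **Sample Characteristics (randomisation steps).** A list of reported pregnancies arrives every month. Families are randomised "based on the updated list of reported pregnancies post-refusal" and wrong-address returns: "The families were thus randomly assigned to either the “intervention” or the “control” group". No block size or within-month ratio is given.
- **Rate of Inclusion.** "The control group was recruited with the same number of participants each month in order to avoid any bias (seasonality, etc" .). The sentence adds a second reason, which is to keep the evaluation visits within the available time. A monthly cap also applies: "When the expected number of families per month (1 per PMI nurse) was reached, recruitment then stopped for that month and resumed the following month".
- **Determination of Sample Size.** The calculation uses "one case per one control, a power of 80%, an alpha risk of 5" %, with a "prevalence rate of 50% in the controls and 25% in the children on the program". This gives 58 per arm, or 64 after allowance for 10% loss.
- **Comparative Analysis.** The Student's t-test "will be used for the comparative analyses of the quantitative variables", and the chi-squared "test will be used for the comparative analyses of the qualitative variables". The Data Analysis section contains no month or period term.

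**The concern.** The design treats time of inclusion as something that could distort the comparison and balances the arms on it. The named tests then pool all months as if that balance did not exist.

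When two arms are balanced on a factor that predicts outcome, the difference between arms no longer carries that factor's variation. A pooled test still counts that variation in its standard error. The standard error is then too large, the true type I error falls below 5%, and some attainable power is not used.

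Period differences are conceivable here. Births ran from September 2018 to December 2019, recruitment paused for four months, and the number of nurses rose from 6 to at least 16. What is at stake is precision in a trial that describes its own sample as small, not the validity of the comparison.

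**Working it through.** **1. The plan's own figure.** With p1 = 0.50, p2 = 0.25, mean 0.375, two-sided alpha 5%, power 80%, pooled variance and no continuity correction:

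n = [1.960 × √(2 × 0.375 × 0.625) + 0.842 × √(0.25 + 0.1875)]² / 0.25² = 57.7, rounded up to **58 per arm**.

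This matches the article. Power is 80.2% at 58 per arm and 84.0% at 64. Sidedness is not stated; two-sided reproduces the figure.

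**2. Quantitative scores, by formula.** Let ρ be the share of outcome variance due to inclusion month, with arms equal in size within month. The true variance of the difference is (1 − ρ) times what the pooled t-test assumes. For an effect that has 80% power when ρ = 0 (1.960 + 0.842 = 2.802 standard errors), in normal approximation:

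- SE overstated by a factor 1/√(1 − ρ)
- type I error, pooled = 2 × [1 − Φ(1.960/√(1 − ρ))]
- power, pooled = Φ(0.842/√(1 − ρ))
- power, month-adjusted = Φ(2.802/√(1 − ρ) − 1.960)

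| ρ (assumed) | SE too wide by | Type I error, pooled | Power, pooled | Power, adjusted |
|---|---|---|---|---|
| 0 | 0% | 5.0% | 80.0% | 80.0% |
| 0.02 | 1.0% | 4.8% | 80.2% | 80.8% |
| 0.05 | 2.6% | 4.4% | 80.6% | 82.0% |
| 0.10 | 5.4% | 3.9% | 81.3% | 84.0% |
| 0.20 | 11.8% | 2.8% | 82.7% | 87.9% |

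**3. Developmental delay (BLR), by simulation.** There were 58 per arm over 12 months, equal arms within month, and a normal month effect on the logit scale. Intercepts were set so that the overall rates stay at the planned 50% and 25%. The comparison is chi-squared v Cochran-Mantel-Haenszel (CMH) stratified by month, both without continuity correction, with 40,000 runs for the power figures at SD 0, 0.5 and 1.0. Twelve months is an assumption: 16 birth months less the 4-month interruption.

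| Month SD, logit (assumed) | Power, chi-squared | Power, CMH | Forgone | Type I error, chi-squared |
|---|---|---|---|---|
| 0 | 79.6% | 79.7% | about 0 | about 5% |
| 0.5 | 80.9% | 82.3% | 1.4 points | 4.4% |
| 0.8 | about 81% | about 84% | about 3 points | 3.7% |
| 1.0 | 82.4% | 86.7% | about 4 points | 3.1% |

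On the observed scale these SDs correspond to a ρ of about 0.06, 0.12 and 0.17. The two approaches agree in direction and size.

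**4. Would broader strata do?** The obvious grouping is by number of nurses, but those dates overlap in Rate of Inclusion. Six nurses for the first 3 months from September 2018 runs to November. Nine for the following 7 months runs to June 2019. Yet ten are counted from May 2019. An assumed four-phase split, with month effects independent of each other, recovers only about 0.4 to 1 point of power at SD 0.5 to 1.0.

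**The case against.** **The tests named are not wrong.** An unadjusted comparison after 1:1 randomisation is valid, and its error here is on the conservative side. This stands in full.

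**A condensed article may leave covariates to an analysis plan that is not shown.** This stands in part. Such a plan could add month, and the absence of detail is no fault. But the article does name the tests, and as named they leave out the factor on which it says the arms were balanced.

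**No month effect is shown.** This stands. No figure is given, and assessing every child at the same ages (4 and 24 months) removes age differences between monthly cohorts. Calendar effects remain possible but unquantified. With a small effect (ρ up to 0.02) less than 1 point of power is at issue, and SDs of 0.8 to 1.0 would be large.

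**Stronger readings that the documents do not support:**

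- *That the trial becomes underpowered.* Holding the within-month odds ratio at 1/3 while the month SD rises gives chi-squared power of about 76%, 71% and 67% at SD 0.5, 0.8 and 1.0. Most of that fall is an artefact. With controls at 50%, the intervention rate drifts to 26.1%, 27.5% and 28.6%, which is no longer the planned 25%, and the stratified test falls too, to about 74% at SD 1.0. At the planned rates the pooled test does not drop below plan.
- *That randomisation itself was blocked by month.* Lists were randomised monthly, but equal numbers are stated only for recruitment, and partly for scheduling reasons. The argument needs only near-balance by month in the families analysed.

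**Conclusion.** The point holds as a minor matter of efficiency. Allocation was made list by list each month and the arms were filled equally by month, so stratifying by month follows the design, and the named pooled tests do not.

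If inclusion month predicts outcome, the pooled tests are mildly conservative: they forgo between nothing and about 4 points of power on developmental delay over month SDs of 0 to 1.0. For scores the figure is at most about 5 points, at ρ = 0.20. If month has no effect, nothing is lost and stratifying costs essentially nothing.

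These sizes rest on assumptions that the documents neither give nor contradict: the month SD (or ρ), 12 active months, independent month effects, and arms that stay balanced by month among the children assessed. There is no bias, no excess of false positives and no shortfall from the planned 80%.

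**What to change.** - **Developmental delay (BLR):** replace the pooled chi-squared test with a CMH test and a risk difference stratified by inclusion month, defined as the monthly list from which the family was randomised.
- **Quantitative scores:** replace the t-test with a linear model with arm and inclusion month as factors. With 116 children and 12 months this leaves 116 − 2 − 11 = 103 residual degrees of freedom, against 114 for the t-test.
- **Sparse months:** CMH copes with strata of 4 to 5 per arm. Combine adjacent months only where a month is uninformative (for example one arm is empty, or all or none of the children are delayed), by a rule set before outcomes are compared. Do not use the nurse-number phases as strata: their dates overlap, and in the assumed split they recover little.

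The cost is analysis wording only. The one data item needed is the monthly list for each family. The article does not say that this is stored as a variable, but the recruitment procedure generates it.

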#### Families Support

##### PERL Support Intervention Group

Following the birth, families in the PERL “intervention” group receive HVs from a PMI nurse divided into three stages: (i) active observation of the baby's development and progress, (ii) playing with the baby, and (iii) listening and talking to the parents (parenting support). The families support is described in Figure 2.

**Figure 2 F2:**
[figure not shown]
Study design of the PERL study.

These HVs take place at predefined intervals (1 HV every month from birth up to the child's 1st birthday, 1 HV every 2 months from 1 to 2 years of age, and 1 HV every 3 months from 2 to 4 years of age) as shown in Figure 2, totaling 26 HVs over 4 years.

The work of PMI nurses is focused on unconditional kindness and availability, enhancing parenting skills, non-directive action, responsiveness to parents' needs and questions, parental contact and support, having a positive approach to situations, and the building of a secure parent/pediatric nurse relationship.

*Particular Case*. Intervention concerns all families residing in the area targeted by the study (universally), irrespective of the make-up of the family (nuclear or single-parent families). Support and assessment will be provided under the same conditions for a single-parent.

At the inclusion stage, the smallest child of the family is included. If during the study a birth should occur in the family, the study will continue without the inclusion of the newborn. Only 1 child in the family is assessed, from birth (4 months) to 4 years.

If other children are present (physically or in conversation), the PMI nurse can meet them: the goal is to respond to parents' requests and to support them throughout their parenthood.

Should the father wish to be present during the HV, they are welcome to do so. Other parents are able to attend HVs should the mother be unavailable; however, the evaluation focuses only on the mother to ensure comparability of certain gender-sensitive tests.

##### Control Group

There is no specific intervention for families in this group, with the exception of the recruitment HV carried out by SB and the two evaluations planned in the study.

While a family in the control group can benefit from monitoring systems should they need to do so (midwife, conventional PMI consultations, maternity hospital, psychological medical center, social worker, and pediatrician, etc.), this is not specifically proposed through the PERL study.

##### Evaluation in Both Groups

To check the initial homogeneity of the groups, we proposed an early comparison of the groups with 10 families from each group, randomly selected by a double-blind process. An independent psychologist assessed the baby's development during the first 30 days after birth.

Two HVs are carried out by SB (and the family's dedicated PMI nurse in the “intervention” group), with the parents, taking place when the child is 4 and 24 months old. The purpose is to assess three things: the child's development, parenting, and parent-child interaction. The assessment tools are described in Table 3.

**Table 3 T3:** Outcome criteria and assessment schedule.

**Instrument**	**Concept measured**	**Validation**	**Outcome assessment place of evaluation**	**Structure of instrument; scoring**	**Time of measurement**				**Group**	
					**0**	**4**	**24**	**4**	**I**	**T**

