#### Socio-Demographic and Family Data

Socio-demographic and family data are collected for both groups: age, level of education, occupation, and family situation, for both parents. For the child: gestational age, gender, birth order within siblings, and birth weight. Information is collected on type of birth, child care arrangements, school attendance, and age on starting school, whether planned or unplanned birth, feeding (breast or bottle), father's involvement in the PERL study, whether or not the family is receiving other support measures, etc. Finally, birth trauma and the presence of any serious psychopathology in the parent will be scored.

During the interview, SB will record how the parent feels about the child, the way the parent sees themselves as a parent, their responses to crying/opposition from the baby, and parent experience of the intervention. SB collects information about how the parents accommodate regular HV from a PMI nurse and how they benefit from this support.

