Family recruitment was completed in December 2019. The fourth month evaluations were completed in July 2020, and 24-month evaluations are currently underway. The first results will be analyzed in 2021, examining the characteristics of the study population, homogeneity of the groups, and the scores on the tests at 4 months. The comparative analysis will begin in 2022, once the 24-month evaluations are completed for both groups. The final comparative analysis will be carried out in 2024–2025, when all the 4 ERTL tests have been carried out by the PMI nurses.

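### A comparison of 10 newborns per group cannot show that the groups are comparable, and the stated 24-month tests make no use of the birth and family data collected in both groups

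*Protocol article*

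**What the plan says.** All references are to the protocol article.

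- **Evaluation in Both Groups** describes the only assessment made at birth: "To check the initial homogeneity of the groups, we proposed an early comparison of the groups with 10 families from each group". An independent psychologist examines these babies within 30 days of birth. In Table 3 the neonatal scale (NBAS) is the only instrument at month 0; every other instrument starts at month 4 or later.
- **PERL Support Intervention Group** sets monthly visits from birth during the first year.
- **Sample Characteristics** places allocation before consent (Zelen, double consent). Families can still refuse after the second letter and at the recruitment visit.
- **Socio-Demographic and Family Data** records, in both groups, age, education, occupation and family situation of both parents, and "For the child: gestational age, gender, birth order within siblings, and birth weight".
- **Comparative Analysis** says that Student's t-test "will be used for the comparative analyses of the quantitative variables" and that the chi-squared test serves for the qualitative ones. No covariate is named there, nor for the Cox model under Longitudinal Assessment.
- **Data Collection** says that, for families who leave before month 4 and cannot be reached, only the fields of the pregnancy notification are available.

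**The concern.** A check of initial homogeneity is useful only if it would reveal an imbalance that matters. Ten babies per group is so few that a non-significant result is the likely outcome even when the groups differ a good deal, so the check can reassure without cause.

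In a trial with consent before allocation this would be a small matter, since randomisation itself protects the comparison. Here the groups analysed are those who stayed after allocation, and refusal may differ by arm. A look at comparability by arm is therefore worth doing properly, on all included families. The data for it are largely collected, and the same variables could sharpen the 24-month comparison. The article itself concedes, under Strengths and Limitations, that the sample may be too small to show a difference on the primary endpoint.

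**Working it through.** **1. The plan's own sample size.** Inputs from Determination of Sample Size: "prevalence rate of 50% in the controls and 25% in the children on the program", 80% power, alpha 5% (taken as two-sided), 1:1 allocation. With the pooled rate p = 0.375:

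n = [1.960·√(2·0.375·0.625) + 0.842·√(0.50·0.50 + 0.25·0.75)]² / 0.25² = (1.342 + 0.557)² / 0.0625 ≈ 57.7, so 58 per group.

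This is the stated figure. For dropout, 58 × 1.10 = 63.8, which gives the stated 64. None of this is disputed.

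**2. What 10 v 10 can detect.** Two-sample t-test, 18 degrees of freedom, noncentrality d·√(n/2) = d·√5, two-sided 5%; approximately normal scores assumed.

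| True imbalance (SD) | Power, 10 v 10 | Power, 64 v 64 |
|---|---|---|
| 0.3 | 10% | 39% |
| 0.5 | 18% | 80% |
| 0.8 | 40% | 99% |
| 1.325 | 80% | about 100% |

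An imbalance of 0.5 SD is thus missed about 81% of the time. For a binary characteristic at 50% v 25%, the size of the trial's own target effect, 10 v 10 has about 20% power by the normal approximation (18% by exact enumeration of the chi-squared test, 9% by Fisher's test).

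**3. How precise the estimate is.** The 95% half-width for a standardised difference is t·√(2/n):

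- 10 v 10: 2.101 × √0.2 = 0.94 SD
- 64 v 64: 1.979 × √(2/64) = 0.35 SD

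The 20 babies are 20/128 = 15.6% of the trial. A finite-population correction, √(1 − 10/64) = 0.92, brings 0.94 only to about 0.86. By chance alone, two groups of 10 differ by 0.5 SD or more about 26% of the time (z = 0.5/√0.2 = 1.118). For 64 v 64 the figure is about 0.5% (z = 0.5/√(2/64) = 2.83). A significant result in the subsample would therefore be nearly as uninformative as a null one.

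**4. Why month 4 is not a baseline.** Monthly visits from birth mean about four visits before the 4-month assessment. Those scores are early outcomes.

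**5. What adjustment could add.** No correlation between baseline variables and outcome is given, so I assume r = 0.3 to 0.5, that is R² = 0.09 to 0.25. For a continuous outcome the equivalent gain in sample size is 1/(1 − R²):

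- R² = 0.09: 1/0.91 = 1.10, so 58 per group act like about 64
- R² = 0.25: 1/0.75 = 1.33, so 58 per group act like about 77

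This formula belongs to a linear model for the quotient. It does not carry over to the powered endpoint, prevalence of delay.

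**6. How many covariates the binary endpoint can bear.** Expected delay events at the design rates: 58 × 0.50 + 58 × 0.25 = 29 + 14.5 = 43.5, about 44. With six covariates and treatment (seven parameters at least) that is about 6 events per parameter; with four covariates and treatment (five), about 9.

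**The case against.** The best defence has four parts.

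- **The 10 + 10 check drives nothing.** No test, threshold or consequence is attached to it. The 2021 analysis under Clinical and Research Implications covers population characteristics and group homogeneity, with no restriction to 20 newborns. This stands, and it limits the harm. The check is nonetheless the one the article describes for initial homogeneity, and it cannot serve that purpose.
- **Homogeneity is not said to be judged on 4-month scores.** A reader might infer it from "homogeneity of the groups, and the scores on the tests at 4 months". The full sentence lists three separate items: characteristics of the population, homogeneity, and 4-month scores. It ties homogeneity to neither of the others, so the text does not support that reading. What remains is a precaution: the 4-month scores should not be used in that way.
- **Unadjusted tests are valid, and covariates may be set in a plan not shown.** Both true. Chance imbalance is already allowed for in the type I error rate, and silence in an article is not a decision to exclude covariates. A reader might infer that the stated tests are biased by their lack of adjustment; that does not follow. The residual point is that the stated method can be improved at little cost.
- **The data are not complete for every family.** A reader might take the section on socio-demographic data to mean full baseline data on all 128. Data Collection rules that out for some early leavers: the notification fields it lists do not include birth weight, gestational age or education. Such families will mostly be absent at 24 months, so the adjusted analysis is little affected, but the baseline table is.

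**Conclusion.** The point holds in a limited form. The 10 + 10 newborn comparison cannot establish comparability: about 18% power at 0.5 SD, and 80% only at about 1.33 SD, assuming normal scores and two-sided 5% tests. That part needs no outside assumption about this trial.

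The part on adjustment is a worthwhile improvement rather than an error. For the quotient it would be worth about 10% to 33% more families if R² lies between 0.09 and 0.25, which the article neither supports nor contradicts. For the binary endpoint the gain should be expected to be smaller, and I put no figure on it. Adjustment addresses only measured differences. Selection through refusal after allocation may also act through unmeasured characteristics, and no full-sample baseline of development exists. The trial is not invalidated, but the changes should be made before the 24-month comparison.

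**What to change.** 1. Do not present the 10 + 10 newborn comparison as evidence of homogeneity; report it descriptively.
2. Report standardised differences by arm, without significance tests, for all included families, using the family and perinatal variables that are fixed by birth. State for each variable how many families lack it, in particular the early leavers.
3. State that the 4-month scores are early outcomes. Do not use them as evidence of baseline balance, nor as covariates in the main 24-month analysis, where they could absorb part of the effect.
4. Make the main 24-month comparison adjusted for a short list fixed before that analysis, for example maternal education, child sex, gestational age and birth order. Use a linear model for the quotient and a covariate-standardised risk difference for delay. Keep the unadjusted test as a sensitivity analysis.
5. Keep the list to about four variables, because only about 44 delay events are expected.

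The cost is a few lines of analysis text and one table; no new data are needed. The real constraints are the missing fields for some early leavers and the small number of events.
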